### ***Analysis of all emergent adverse events***

The following emergent adverse event summaries will be generated:

- Overview of emergent adverse events, summarizing number (%) of participants with at least one event and number and rate per patient-year for:
  - Pre-emergent adverse event
  - Emergent adverse event
  - Serious emergent adverse event
    - Death,
    - In-patient hospitalization
    - Life threatening illness or accident,
    - Permanent disability or incapacity
    - Other serious illness that might have results in an SAE without aggressive medical intervention
  - Emergent unexpected event that may be related to study procedures
  - Emergent adverse event that occurred while under the supervision or guidance of study related personnel
    - AE that meets criteria for SAE
    - Event requiring active intervention by research staff to reduce potential harm
    - Chest pain for more than two minutes after stopping exercise
    - Dyspnea for more than two minutes after stopping exercise
    - Vital signs out of range (systolic BP  $\geq 250$  mmHg or diastolic  $\geq 115$  mmHg, HR  $>120$  beats/minute or  $< 45$  beats/minute) for more than two minutes after stopping exercise
    - A fall during study recommended activity
    - A symptom or illness that developed and required medical management or attention

- Emergent adverse event of special interest
  - Emergency room or urgent care visit
  - Fracture
  - Outpatient surgery
  - Abnormal laboratory or diagnostic test result requiring immediate medical attention
  - Restricted activity due to health problem potentially related to the study activity that led an inability to leave home for at least one week
- All emergent adverse events by primary SOC, HLGT, HLT, and PT, showing number (%) of participants with at least 1 emergent adverse event and number of events and rate per patient-year sorted by the SOC internationally agreed order. The other levels (HLGT, HLT, PT) will be presented in alphabetical order
- All emergent adverse events by primary SOC and PT, showing the number (%) of participants with at least 1 emergent adverse event and number of events and rate per patient-year, sorted by the internationally agreed SOC order and by decreasing incidence of PTs within each SOC in the MCI group.

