#### **6.2.1.2. Mode and Frequency**

The PA component is designed to be performed both at the centre and at home. During the intervention, participants will train at the centre twice a week under direct supervision of instructors. The supervised setting will allow instructors to better tailor the programme to individual needs and abilities, so as to prevent early dropout and facilitate the building of self-efficacy and support, which have been found to be key to long-term PA maintenance.

As shown in the PA schedule reported below, centre-based sessions will be supplemented, in a progressive fashion, with home-based exercises as a means of facilitating PA in multiple settings, adopting a healthier behaviour, and promoting long-term adherence. The home-based sessions could be replaced by an additional centre-based session if the participant is not compliant at home or prefers returning to the centre.

The total amount of PA will be monitored on a continuous basis by the AdamoWatch (see Chapter 7 "Information and Communication Technology"). At specified timeframes (at baseline and every 6 months) and on-demand by the investigator, the study staff will monitor the adherence to PA using such information and provide personalised feedback/tips to the participant. As back-up plan and in support of the AdamoWatch, investigators will also have results of actimetry from the ActivPALTM device (measured at baseline and every 6 months [ $\pm 2$  weeks]).

| Intervention staff contacts for the PA group |                        |                                                                                          |
|-----------------------------------------------------|------------------------|------------------------------------------------------------------------------------------|
| Week                                         | Centre-based PA | Home-based PA                                                                     |
| Adoption
(weeks 1-52)                     | 2 times each week      | 1 time/week (weeks 1-4)
2 times/week (weeks 4-8)
Up to 3-4 times/week (weeks 8-52) |
| Maintenance
(weeks 53 – end of the trial) | 2 times each week      | Up to 3-4 times/week                                                                     |

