#### **6.3.1. Mode and Frequency**

The HALE programme arm will meet in small groups (approximately 10-20 participants per group), two times per month with required participation at least once per month. Telephone calls will be made after missed contact to problem-solve barriers to attendance and encourage regular participation. As undertaken in the LIFE study, those participants randomised to the HALE programme will receive an individual 45-minute introductory session, by a health educator, during which time the programme is described and questions are answered.

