rare instances, heart attack, stroke, and death. Cardiovascular events are assessed using standard protocol measures including ECGs. When a cardiovascular event has occurred, the study physician decides whether it is permissible for the participant to continue interventions. If the SPRINTT interventions are discontinued for safety reasons, they may be resumed after consultation with the participant's primary care physician.

Serious fall injuries and fractures are assessed using standard protocol measures, including radiographs and hospital records. When a serious fall injury or fracture occurs, a study physician decides whether it is permissible for the participant to continue interventions. If the SPRINTT interventions are discontinued for safety reasons, they may be resumed after consultation with the participant's primary care physician.

In the SPRINTT safety monitoring system, participants who report adverse events to any staff person at any time are referred to unblinded medical staff responsible for identifying, recording, and managing these events. Safety-related events are reported in a timely fashion as required by the DSMB and the Ethics Committee responsible for the study. Interventionists and other staff reporting or managing adverse events for safety purposes do not at any time communicate information regarding these events to study assessment personnel.

SPRINTT maintains an event outcome record that is completely separate and distinct from the safety monitoring system for the intervention group. This is necessary because many of the SPRINTT staff members are not masked to intervention assignment, and it is critical that the identification and reporting of serious adverse events for safety reasons not bias the study's collection of outcome data. Thus, for outcome purposes, all SPRINTT participants are systematically queried at clinic visits or phone calls according to the protocol to capture outcome data on study outcomes, medical events, or adverse experiences. This separate outcome record contains solely those adverse events that are reported through these interviews conducted by designated outcome assessment staff masked to intervention assignment.

All serious adverse events and deaths shall be reported within 48 hours to DSMB and to the Management Board. All Serious Adverse Events shall be reported in a summary format by the blinded treatment arm (A and B) to the DSMB and Management Board monthly.

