#### 2.1.4.1 Adverse events variables

The following adverse events (AE) are to be collected during the study:

- Serious AEs,
- Unexpected AEs that may be related to study procedures,
- AEs that occurred while under the supervision of guidance of study related personnel
- AE of special interest (AESI)

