### ***Rate of adverse events per patient-year***

Computed as [sum of number of events for all analysis population] / [sum of patient-year of study participation for all analysis population], with patient-year of study participation calculated per participant as number of days from date of randomization visit V1-T0 (or date of randomization if V1 is missing) to end date of study participation as reported by investigators in the End of study e-CRF page divided by 365.25.

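### The supervised-AE and pooled all-EAE tables are not directly comparable between arms, because supervision is a collection route and MCI has several times as many supervised sessions as HALE

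*Combined protocol and SAP*

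**What the plan says.** **Collection.** SAP 2.1.4.1 opens its list with "The following adverse events (AE) are to be collected during the study" and gives four routes: serious events; "Unexpected AEs that may be related to study procedures"; "AEs that occurred while under the supervision of guidance of study related personnel"; and events of special interest (AESI). Three items in the supervised category (chest pain, dyspnoea, out-of-range vital signs) are defined by persistence after exercise stops, and another is a fall during activity that the study recommends. Four of the five AESI items (emergency or urgent care visit, fracture, outpatient surgery, abnormal test needing immediate attention) require neither supervision nor a link to the study.

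**Exposure to supervision.** In MCI, "participants will train at the centre twice a week under direct supervision of instructors" (Protocol 6.2.1.2), and the schedule keeps this frequency to the end of the trial. HALE groups meet "two times per month with required participation at least once per month" (Protocol 6.3.1), with 5-10 minutes of upper-limb stretching or relaxation per class. Protocol 11.7 has blood pressure and heart rate checked around the walking activity at every centre session; no counterpart is described for HALE.

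**Reporting.** SAP 2.4.5.1 reports the supervised category, listed as "Emergent adverse event that occurred while under the supervision or guidance of study related personnel", and all emergent events pooled, by arm. It uses percentages of participants and rates whose denominator is the "sum of patient-year of study participation for all analysis population" (SAP 2.5.1), that is, days in the study divided by 365.25. SAEs, AESIs, supervised events and procedure-related events each also have their own table.

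**Other data.** SAP 2.4.3 has attended and expected sessions recorded monthly in both arms. Protocol 11.9 describes an outcome record separate from safety monitoring: "This separate outcome record contains solely those adverse events that are reported through these interviews conducted by designated outcome assessment staff masked to intervention assignment". The SAP does not say which of the two streams feeds its AE tables.

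**The concern.** A non-serious event that is neither on the AESI list nor unexpected and possibly procedure-related enters the database only if it happened under staff supervision or guidance. The chance of meeting that condition is set largely by how often the participant is with staff, and the assigned programme decides that. Dividing by calendar time does not correct for it, and percentages of participants with an event are affected in the same way.

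SAP 2.4.5.1 puts the main emphasis of AE reporting on emergent events, so the pooled tables are the ones most likely to be read as the summary of harm. A reader who sees more events in MCI could not tell harm from exercise apart from closer observation. The protocol synopsis lists the safety and tolerability of both interventions as an objective, so the distinction matters.

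**Working it through.** The documents state no AE rate or contact ratio, so there is no plan figure to reproduce.

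**Step 1: scheduled sessions per year.**
- MCI: 2 per week × 52 = 104.
- HALE offered: 2 per month × 12 = 24. HALE required: 1 per month × 12 = 12.
- Ratio k: 104/24 = 4.3; 104/12 = 8.7.

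**Step 2: with imperfect MCI attendance.** Protocol section 12 quotes 60-85% adherence to physical training in earlier long-term trials.
- 60%: 62.4 sessions; 62.4/24 = 2.6 and 62.4/12 = 5.2.
- 85%: 88.4 sessions; 88.4/24 = 3.7 and 88.4/12 = 7.4.

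These figures count sessions, not hours, because HALE meeting length is not given. Assessment visits follow the same schedule in both arms and are left out. Counting the three of the first year (months 3, 6 and 12) gives 107/27 = 4.0 and 107/15 = 7.1. Home sessions are also left out, because the SAP does not say whether they count as guidance.

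**Step 3: the supervised-AE table.** Assume the same event risk per session in both arms. The rate ratio per patient-year then equals k, 4.3 to 8.7 at full schedule, while the ratio per attended session is 1.0 by construction. The percentages move too. At an illustrative 0.001 events per session over 2 years, the proportion with at least one event is 1 − exp(−2 × sessions per year × 0.001):
- MCI: 1 − exp(−0.208) = 18.8%.
- HALE at 24 a year: 1 − exp(−0.048) = 4.7%; at 12 a year: 1 − exp(−0.024) = 2.4%.

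**Step 4: the pooled all-EAE tables.** Let s be the share of HALE events captured only through supervision (assumed; not in the documents). With no true difference per session and equal rates for everything else, the pooled rate ratio is (1 − s) + s × k.

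| s | k = 2.6 | k = 4.3 | k = 8.7 |
|---|---|---|---|
| 1% | 1.02 | 1.03 | 1.08 |
| 5% | 1.08 | 1.17 | 1.38 |
| 10% | 1.16 | 1.33 | 1.77 |
| 25% | 1.40 | 1.83 | 2.92 |

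**Step 5: what this route leaves alone.** SAEs, deaths and the four AESI items named above qualify whether or not staff were present, so s is zero for them and the ratio through this route stays at 1.

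**The case against.** The strongest reply has four parts.

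1. **Collection is wider than supervision.** The AESI route takes in many non-serious events without any contact, and falls since the last visit are asked of everyone on the Outcome events form (SAP 2.1.4.2). This stands. A reader might infer that most non-serious events enter only through supervision; the documents give no AE counts, so that cannot be shown.

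2. **The main safety information is reported separately.** SAEs, AESIs and deaths have their own analyses, time to death is the only safety outcome formally tested between arms, and the separate supervised table lets a reader see whether that category drives a difference. This stands, and it confines the problem to two comparisons. It does not remove it: the supervised table carries the same calendar denominator, and no all-EAE summary free of the contact route is planned.

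3. **The effect may be negligible.** With s at 1% the pooled ratio is 1.03 to 1.08. This is possible, but the plan gives no means of knowing which row of the table applies.

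4. **Frequent exercise is the assigned treatment.** Events per patient-year by randomised arm answer a proper question about the yearly burden of each programme. A per-session rate conditions on attendance after randomisation, and could return a ratio near 1 even if 104 sessions a year cause more events in total. This stands fully. It rules out replacing the patient-year rate or dropping events, but not adding tables.

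**Conclusion.** The supervised-AE table and the pooled all-EAE tables are not directly comparable between arms, and can show an MCI excess with no difference in risk per session. For the supervised table the ratio from scheduled sessions alone is 4.3 to 8.7, or 2.6 to 7.4 at 60-85% MCI adherence with HALE at 24 or 12 meetings. This rests on equal risk per session, which is an assumption when exercise training is set beside a workshop. For the pooled tables the size is unknown; 1.03 to 2.92 covers assumed shares of 1% to 25% at the scheduled ratios.

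A reader might go further and infer that the safety comparison as a whole will show excess MCI harm from contact alone. The documents do not support that. SAEs, deaths and the four contact-independent AESI items are outside this route, the pooled effect depends on an unstated share, and a true exercise effect would appear in the same supervised category. Nor can it be said that the masked record is unused, since the SAP is silent on the source of its AE data. The point is an inexpensive improvement to the safety reporting and leaves the primary analysis untouched.

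**What to change.** In SAP 2.4.5.1, keep every planned patient-year table and add:

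1. The supervised-AE category per 100 attended sessions by arm, using the attended-session counts of SAP 2.4.3.
2. A supplementary between-arm all-EAE table that leaves out non-serious events recorded solely because they occurred under supervision. Those events stay in the existing supervised-AE table.
3. A statement that the between-arm AE interpretation rests on SAEs, deaths, the contact-independent AESIs and the supplementary table. The masked outcome record of Protocol 11.9 can support this only if it holds AE data that can be coded; the documents do not show that it does.

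**Cost.** Some SAP wording and a few extra tables from data already planned for collection. The per-session rate conditions on attendance and handles home sessions only approximately, so it supplements the patient-year rate and does not replace it. The supplementary table will still contain events from the procedure-related route and the fifth AESI item (restricted activity), both of which turn on a judged link to the study; a footnote should say so.

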***Analysis of all emergent serious adverse event(s)***

- All emergent serious adverse, by primary SOC and PT for each subcategory, showing the number (%) of participants and number of events and rate per patient-year, sorted by the internationally agreed SOC order and by decreasing incidence of PTs within each SOC in the MCI group for each subcategory.

***Analysis of emergent adverse events of special interest***

- All emergent adverse events with special interest, by primary SOC and PT for each subcategory, showing the number (%) of participants and number of events and rate per patient-year, sorted by the internationally agreed SOC order and by decreasing incidence of PTs within each SOC in the MCI group for each subcategory.

***Analysis of emergent adverse events occurred under the supervision of study-related personnel***

- All EAE for AE occurred under the supervision of study-related personnel, by primary SOC and PT for each subcategory, showing the number (%) of participants and number of events and rate per patient-year, sorted by the internationally agreed SOC order and by decreasing incidence of PTs within each SOC in the MCI group for each subcategory.

***Analysis of emergent adverse events unexpected related to study procedures***

- All EAE for unexpected AE related to study procedures, by primary SOC and PT, showing the number (%) of participants and number of events and rate per

patient-year, sorted by the internationally agreed SOC order and by decreasing incidence of PTs within each SOC in the MCI group.

#### **2.4.5.2 Falls**

- Emergent injury falls by primary by primary SOC, HLT and PT, showing the number (%) of participants and number of events and rate per patient-year, sorted by the SOC internationally agreed order. The other levels (HLT, PT) will be presented in alphabetical order.

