##### **4.3.2. Secondary outcomes**

- a. Changes in physical performance measures
  - Short physical performance battery (SPPB)
  - Handgrip strength
  - Usual gait speed
- b. Changes in disability status
  - Pepper Assessment Tool for Disability (PAT-D)
  - Incidence of persistent mobility disability (operationalised as the failure of completing the 400-metre walk test in two consecutive 6-month visits)
- c. Changes in body composition measures (assessed using Dual Energy X-Ray Absorptiometry, DXA), anthropometric parameters (e.g., body mass index, mid-arm circumference, calf circumference), and nutritional status (Mini Nutritional Assessment-Short Form, MNA-SF)
- d. Changes in cognitive function (assessed using Mini Mental State Examination, MMSE) and mood (i.e., Center for Epidemiological Studies-Depression scale, CES-D)

- e. Incidence of falls (assessed using self-reported questionnaire as well as via a technological device) and injurious falls
- f. Modifications of quality of life (measured using the EuroQoL-5D instrument)
- g. Differences in use of healthcare services (e.g., outpatient clinics, emergency room admissions, hospitalisations, institutionalisations)
- h. Mortality rate

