### 10.2.1. Primary efficacy endpoint

The primary comparison of intervention groups with respect to the distribution of time until the first post-randomisation occurrence of the primary outcome will be based on log-rank stratified by study site and gender. The primary comparison will be conducted only in study participants with baseline SPPB  $< 8$ . If this primary analysis is statistically significant ( $p < 0.05$ ), the comparison will be extended to include the remaining 300 participants with baseline SPPB 8-9. An additional binary indicator variable will be introduced denoting a baseline SPPB score  $< 8$  or  $\geq 8$  and its interaction with the intervention group. Hazard ratio and confidence interval will be computed for the whole population only if this interaction term can be ignored (i.e., if it is not statistically significant). The hazard ratio between intervention groups and the corresponding confidence interval will be computed using a Cox proportional hazard model with site and gender as co-variables for comparison in subjects with a SPPB score  $< 8$  and by adding

the SPPB score  $\geq 8$  flag and corresponding interaction term as co-variables for the comparison in the whole study population.

The time to event is defined as the time from randomisation to the date of first occurrence of disability. Participants who do not meet this criterion will be censored at the time of their last primary outcome evaluation. In secondary analyses, in order to take into account additional covariates, we will use a Cox proportional hazards model if the underlying assumptions appear warranted. The proportional hazards assumption will be verified by testing the treatment-by-time interaction in the Cox model.

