### **10.2.2. Secondary efficacy endpoints**

For the assessment of secondary efficacy endpoints, specific models will be used for continuous outcomes (e.g., changes in physical performance, nutritional status, functional status, cognitive function, and quality of life). Specifically, changes over time between groups will be assessed by a repeated-measure mixed model with terms for intervention, time, baseline score, baseline score by intervention interaction, and time by intervention interaction. For outcomes such as incidence of falls and mortality rate, the analysis defined for the primary efficacy outcome will be replicated (except for the secondary analysis with competitive risk for the mortality rate). Additional analyses (e.g., subgroup composite endpoint analyses) will be defined in agreement with the Managing Board and the Data Safety Monitoring Board and specified in the statistical analysis plan that will be produced prior to the beginning of the analyses.

Please note that within this section, we have limited the description of the analysis plan to the major SPRINTT hypotheses. Nevertheless, the relevance and amount of the data collected during the project will certainly lead to ancillary and secondary analyses always within the scopes and objectives of SPRINTT. Such secondary plans will be developed after formal approval and validation by the Managing Board of SPRINTT.

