## 1.5 MODIFICATIONS TO THE STATISTICAL SECTION OF THE PROTOCOL

This section summarizes major changes to the protocol statistical section with emphasis on changes after study start (after the first participant was enrolled).

The statistical section of the protocol was not changed in an amendment

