#### **2.1.4.2 Falls**

Falls will be described using information collected in the Outcome events eCRF form:

- Since the last visit, participants who broke a bone as a result of a fall (Yes/No/Refused/Don't know)
- Since the last visit, participants who fallen, and participants who fallen resulting in an inability to leave home for at least one week (Yes/No/Refused/Don't know)

Injury falls will be identified using a customized MedDRA searches

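### The SAP drops, without declaring it, the between-arm comparison of falls that the protocol specifies, and gives the visit-reported fall data no table or test

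*Combined protocol and SAP*

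**What the plan says.** **Protocol.** Section 4.3.2 lists as a secondary outcome "Incidence of falls (assessed using self-reported questionnaire as well as via a technological device) and injurious falls". Section 10.2.2 fixes the method: "For outcomes such as incidence of falls and mortality rate, the analysis defined for the primary efficacy outcome will be replicated". The analysis to be replicated is in section 10.2.1. It is restricted first to baseline SPPB below 8, it "will be based on log-rank stratified by study site and gender", and a Cox model supplies the hazard ratio and confidence interval. The synopsis says the same.

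**SAP.**
- Section 1.2.2 keeps falls and injurious falls among the secondary objectives.
- Section 2.1.3.2, the list of secondary efficacy endpoints, omits falls. They appear under safety instead.
- Section 2.1.4.2 names two sources. The first is the visit form: "Falls will be described using information collected in the Outcome events eCRF form". Its items, asked since the last visit, are any fall, a bone broken in a fall, and a fall that kept the participant at home for at least a week. The second is a MedDRA search for injury falls.
- Section 2.4.5.2, the falls analysis, holds one item: "Emergent injury falls by primary by primary SOC, HLT and PT", with participants, events and rate per patient-year.
- Section 2.4.5.3 gives time to death a log-rank test stratified by site and gender, a Cox hazard ratio with 95% CI, and cumulative incidence curves.
- Section 1.6, where the SAP would list its own statistical modifications, has no entry.

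**The concern.** A secondary objective with an analysis method fixed in the protocol reaches the SAP without that method. The one table that is specified gives counts and rates by arm, with no effect estimate and no measure of uncertainty. Whether an exercise programme changes falls in frail older people is a question readers will put to this trial. Without a planned comparison, anything reported will be informal or chosen after the data are seen.

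A second, weaker concern is the source of that table. Adverse events are collected selectively, and one of the four collected categories in SAP 2.1.4.1 is "AEs that occurred while under the supervision of guidance of study related personnel". That category expressly includes falls during activity the study recommends. The multicomponent arm (MCI) has much more supervised contact and recommended activity than the education arm (HALE), so some falls may have a better chance of being recorded in MCI.

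**Working it through.** **1. Is the comparison missing, and is the omission specific to falls?** Protocol 10.2.2 names falls and mortality in one sentence and gives both the same analysis. The SAP moves both to safety.

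| Item | Falls | Mortality |
|---|---|---|
| Protocol 10.2.2 | replicate primary analysis | replicate primary analysis |
| Place in the SAP | safety, 2.4.5.2 | safety, 2.4.5.3 |
| Stratified log-rank | none | yes |
| Cox hazard ratio with 95% CI | none | yes |
| Cumulative incidence curves | none | yes |
| Change listed in SAP 1.6 | none | none needed |

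The move to safety therefore does not explain the loss, because mortality made the same move and kept its analysis.

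**2. Is the change declared?** SAP 1.5 says "The statistical section of the protocol was not changed in an amendment". That concerns protocol amendments and does not bear on whether the SAP agrees with the protocol. Section 1.6 is the relevant place, and it lists nothing.

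**3. What is specified for the visit-form data?** SAP 2.1.4.2 says they will be described. SAP 2.4.5 says safety summaries are by arm. Section 2.4.5.2 then gives no table, test or estimate for the three form items. Device-detected falls, part of the outcome in protocol 4.3.2, appear in neither falls section.

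**4. Planned contact by arm** (protocol 6.2.1.2 and 6.3.1; SAP 1.4).
- MCI centre sessions: 2 a week × 52 = 104 a year.
- HALE meetings offered: 2 a month × 12 = 24 a year, a ratio of 104/24 = 4.3. Required: 1 a month = 12 a year, a ratio of 104/12 = 8.7.
- MCI centre plus 3 to 4 home sessions a week: 5 × 52 = 260 to 6 × 52 = 312 a year.

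These are ratios of contact, not of capture. The observed rate ratio equals the true rate ratio times (capture in MCI / capture in HALE), and the documents give neither capture probability. Assuming 90% in MCI and 70% to 90% in HALE, a true ratio of 1.0 would show as 0.90/0.90 = 1.00 up to 0.90/0.70 = 1.29. That range is only the assumption restated, and it includes no bias.

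**5. Would the promised comparison be informative?** The documents give no power figure for falls. The primary figure serves as a check on the formula. Events = 4(z₀.₉₇₅ + z₀.₈₅)² / (ln HR)² = 4(1.960 + 1.036)² / (ln 0.75)² = 434, which matches protocol 10.1.

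For falls, take the 1,205 randomised participants with SPPB below 8 (SAP 1.3) and an **assumed** share with a first reported fall. Power = Φ(√events × |ln HR| / 2 − 1.960).

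| Assumed share with a fall | Events | Power, HR 0.80 | Power, HR 0.75 |
|---|---|---|---|
| 20% | 241 | 0.41 | 0.61 |
| 30% | 362 | 0.56 | 0.78 |
| 40% | 482 | 0.69 | 0.88 |
| 50% | 602 | 0.78 | 0.94 |
| 60% | 723 | 0.85 | 0.97 |

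The comparison is feasible, and over much of this range it is informative.

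**The case against.** Several points on the other side are fair.

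- **The adverse-event table is not the only planned fall result.** A reader might infer that it is. SAP 2.1.4.2 does not support that: falls from the Outcome events form are to be described. The gap is that no table layout, test or estimate is specified for them.
- **The trial is not unable to address falls.** A reader might infer this too. Fall questions are put to both arms on the same visit schedule (protocol 6.1 and 7.3), and by-arm description is planned. What is missing is the analysis.
- **Capture that depends on arm is an inference.** Serious events, fractures and emergency visits are defined alike in both arms, and protocol 11.9 has participants report adverse events at scheduled contacts. Only the supervised and study-activity routes depend on contact, and SAP 2.4.5.1 tabulates supervised events separately, so a reader can see that component. A fall during prescribed exercise is also a real consequence of the intervention.
- **The visit form is not free of bias.** Protocol 11.9 describes an outcome record drawn from "interviews conducted by designated outcome assessment staff masked to intervention assignment", but does not say that the Outcome events form is that record. Participants know their arm and the items are self-reported.
- **Secondary efficacy endpoints are exploratory** (SAP 2.4.4.3), so no confirmatory claim rests on a falls p-value.

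All of this limits the ascertainment argument to a caveat. None of it supplies the comparison in protocol 10.2.2 or explains why mortality kept its analysis and falls did not.

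**Conclusion.** The point holds in this form: the SAP omits, without recording it, the between-arm analysis of falls that the protocol specifies. As written, it provides no hazard ratio, confidence interval or test for a stated secondary objective. This rests on the text alone and needs no assumption.

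The ascertainment concern is secondary. The contact ratio of 104 to 24 a year makes uneven capture plausible for one adverse-event route and, if it operates, it would tend to count against MCI. The documents establish neither its presence nor its size, and no bias is compatible with them. The power figures rest on assumed fall proportions and show feasibility only.

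The change should be made, because it restores an estimate the protocol promised. It does not affect the primary result.

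**What to change.** In SAP 2.4.5.2, add the following, labelled exploratory:

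1. **Endpoint.** Time from randomisation to the first visit at which any fall is reported on the Outcome events form. Separately, time to the first visit at which a fall with a fracture, or with at least a week unable to leave home, is reported.
2. **Analysis.** In randomised participants with baseline SPPB below 8, a log-rank test stratified by site and gender, with a Cox hazard ratio and 95% CI.
3. **Censoring and death.** Censor at the last visit with the form completed. State whether death before a fall is a competing event or a censoring. This must be explicit, because the primary endpoint in SAP 2.1.3.1 counts death as an event and literal replication would carry that into the falls endpoint.
4. **Sensitivity.** An interval-censored analysis, since a yes/no answer since the last visit places the fall only within a visit interval.
5. **Existing table.** Keep the adverse-event table as safety description, with a note that its capture may differ by arm.
6. **Record.** List in SAP 1.6 any remaining departure from protocol 10.2.2, and say there what will be done with device-detected falls.

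The cost is SAP wording and a small set of extra output from data already collected. The downsides are coarse timing and, because the form items are yes/no, no analysis of recurrent falls from this source.
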